## Abstract

**Background:**

Whereas lowering the intraocular pressure (IOP) can slow optic nerve degeneration in glaucoma, many patients with glaucoma continue to develop progressive loss in vision despite a significant reduction in IOP. No treatment has been shown to be effective for neuroprotection in glaucoma. We set out to conduct a randomized controlled trial to investigate whether nicotinamide riboside (NR), a nicotinamide adenine dinucleotide precursor, is effective to slow optic nerve degeneration in patients with primary open-angle glaucoma (POAG). We hypothesize that patients treated with NR have a slower rate of progressive retinal nerve fiber layer (RNFL) thinning compared with those treated with placebo.

**Methods:**

This is a randomized, double-blind, placebo-controlled, parallel-group, multi-center study including 125 patients with POAG. Patients will be randomized to receive 300 mg NR or placebo for 24 months. Clinical examination, optical coherence tomography imaging of the RNFL, and visual field (VF) test will be performed at the baseline, 1 month, 4 months, and then at 2-month intervals until 24 months. The primary outcome measure is the rate of RNFL thinning measured over 24 months. The secondary outcome measures include (1) time to VF progression, (2) time to progressive RNFL/ganglion cell inner plexiform layer (GCIPL) thinning, and (3) the rate of change of VF sensitivity over 24 months (to investigate neuroprotection) and 1 month (to investigate neuroenhancement). The rates of RNFL thinning and VF sensitivity decline between treatment groups will be compared with linear mixed modeling. Survival analysis will be performed to compare the differences in time from baseline to VF progression and time from baseline to progressive RNFL/GCIPL thinning between treatment groups using Cox proportional hazards models.

**Discussion:**

Outcome measures in glaucoma neuroprotection trials have been centered on the detection of VF progression, which may take years to develop and confirm. In addition to addressing whether NR has a neuroprotective/neuroenhancement effect in glaucoma patients, this study will demonstrate the feasibility of studying neuroprotection in a relatively short trial period (24 months) by comparing the rates of progressive RNFL thinning, a more reproducible and objective outcome measure compared with VF endpoints, between treatment groups.

**Trial registration:**

Chinese Clinical Trial Registry 1900021998

## Administrative information

Note: the numbers in curly brackets in this protocol refer to SPIRIT checklist item numbers. The order of the items has been modified to group similar items (see http://www.equator-network.org/reporting-guidelines/spirit-2013-statement-defining-standard-protocol-items-for-clinical-trials/).

## Introduction

### Background and rationale {6a}

Glaucoma, characterized by progressive degeneration of the optic nerve or the axons of retinal ganglion cells, is the leading cause of irreversible blindness worldwide with 76 million patients worldwide in 2020 [1, 2]. Although lowering the intraocular pressure (IOP) can decrease the rate of visual field (VF) sensitivity worsening, many patients with glaucoma continue to show a progressive loss in vision despite a significant reduction in IOP [3, 4]. The need to investigate treatment to protect the optic nerve other than IOP reduction is pressing. At present, there is no neuroprotective therapy approved for the treatment of glaucoma.

Nicotinamide riboside (NR) is a precursor of nicotinamide adenine dinucleotide (NAD), which is a key cofactor in redox metabolism including glycolysis, citric acid cycle, and oxidation phosphorylation as well as in non-redox cell signaling and gene regulation [5–7]. Increasing evidence has shown that axon degeneration is associated with a decline in NAD and that supplementation of NAD or NAD precursors is effective to delay axon degeneration in vitro and in vivo [7–10]. In an experimental study, Williams and colleagues demonstrated oral administration of nicotinamide was able to increase the levels of NAD in the retina and protect retinal ganglion cells from degeneration in a mouse model of glaucoma [11]. Remarkably, 93% of eyes did not develop glaucomatous retinal ganglion cell loss despite elevated IOP in animals treated with a high dose of oral nicotinamide (2000 mg/kg/day). However, high-dose nicotinamide can induce hepatotoxicity and painful flushing [12]. Nicotinamide riboside, by contrast, is more orally bioavailable than nicotinamide to increase tissue levels of NAD [6]. It is a well-tolerated NAD precursor with a high safety profile [13, 14]. Although oral administration of NAD precursors affords protection against glaucoma and neurodegenerative diseases in animal models, lost in translation to clinical practice is common in neuroprotection studies [15, 16]. We set out to perform a randomized controlled trial to determine whether NR can protect the optic nerve in patients with glaucoma.

## Objectives {7}

The study aims to investigate if oral supplementation of NR is effective to decrease the rate of progressive retinal nerve fiber layer (RNFL) thinning in glaucoma.

## Trial design {8}

This study is a double-blind, parallel-group (1:1), randomized, controlled, superiority trial. The trial will randomize 125 patients with primary open-angle glaucoma (POAG) with evidence of progressive RNFL thinning or ganglion cell inner plexiform layer (GCIPL) thinning in optical coherence tomography (OCT) without visual field (VF) progression in at least one eye to receive oral NR 300 mg/day or placebo. Patients will be followed up at 1 month, 4 months, and then every 2 months until 24 months for comparisons of the rates of RNFL thinning and the rates of change of VF sensitivity between treatment groups. The same IOP-lowering regimen as prescribed before study recruitment will be provided throughout the 24-month study period unless a safety endpoint (described below) is reached. Change in VF sensitivity at 1 month will be compared between treatment groups to investigate neuroenhancement. We hypothesize that patients treated with NR have a slower rate of RNFL thinning and a slower rate of VF sensitivity decline compared with those treated with placebo over 24 months and that an improvement in VF sensitivity could be detected in the NR-treated group at 1 month. The study flow chart is shown in Fig. 1.

**Fig. 1 Fig1:**
[figure not shown]
Flow chart of the study design. *POAG* primary open-angle glaucoma, *RNFL* retinal nerve fiber layer, *GCIPL* ganglion cell inner plexiform layer, *GPA* Guided Progression Analysis, *TPA* Trend-based Progression Analysis, *EMGT* Early Manifest Glaucoma Trial, *IOP* intraocular pressure, *VF* visual field, *OCT* optical coherence tomography, *NR* nicotinamide riboside

## Methods: participants, interventions, and outcomes

### Study setting {9}

Patients with primary open-angle glaucoma will be consecutively recruited from Hong Kong Eye Hospital, Chinese University of Hong Kong (CUHK) eye clinic, and Prince of Wales Hospital eye clinic. These patients will be followed up at the CUHK eye clinic and the University of Hong Kong Glaucoma and Optic Nerve Diagnostic Center for clinical examination, OCT imaging and VF testing.

### Eligibility criteria {10}

Inclusion criteria are as follows: age ≥ 18 years, best corrected VA ≥20/40, IOP ≤28 mmHg, and evidence of progressive RNFL/GCIPL thinning detected by Guided Progression Analysis (GPA, Carl Zeiss Meditec) or Trend-based Progression Analysis (TPA) in one or both eyes [17–20]. Exclusion criteria are as follows: VF progression detected by the Early Manifest Glaucoma Trial (EMGT) criteria (likely progression in GPA) [21] over 18 months prior to study enrollment, pathological myopia, diseases that may cause visual field loss or optic disc abnormalities other than glaucoma, inability to perform reliable visual field, suboptimal quality of OCT images, diabetic retinopathy/maculopathy, and a history of abnormal liver function within 12 months.

### Who will take informed consent? {26a}

The principal investigator will take informed consent after explaining the potential benefits and downsides of participation, the details of clinical investigations performed during the study follow-up, and the right to withdraw from the study. Patients will be given at least 1 week to consider the participation and raise any questions at their concern.

### Additional consent provisions for collection and use of participant data and biological specimens {26b}

This trial does not involve collecting biological specimens for storage.

## Interventions

### Explanation for the choice of comparators {6b}

Patients randomized to the control arm will be provided a placebo containing corn starch. The placebo capsule has identical color, appearance, and packaging as the capsule containing NR.

### Intervention description {11a}

During the 24-month study period, patients randomized to the NR treatment group will have oral administration of 3 capsules of NR every morning (each capsule containing 100 mg NR); patients randomized to the controlled group will have oral administration of 3 capsules of placebo every morning. Patients will be followed up at 1 month, 4 months, and then every 2 months for clinical examination, VF testing, and OCT imaging of the RNFL/GCIPL.

### Criteria for discontinuing or modifying allocated interventions {11b}

The safety endpoints are (1) development of VF progression (likely progression in GPA according to the EMGT criteria) [21], (2) decrease in visual acuity ≥2 lines, and (3) IOP > 30 mmHg on 2 consecutive visits. Patients will exit the study and receive appropriate treatment if any of the safety endpoints is reached. Patients are allowed to withdraw from the study for any reasons at any time.

### Strategies to improve adherence to interventions {11c}

The capsules (NR or placebo) are packed in weekly packets (each packet contains 21 capsules—3 capsules per day for 7 days) labeled with patient’s name. Patients are requested to bring back the packets at each follow-up visit. Capsules left in the packets will be counted to check and remind patients’ compliance to the treatment.

### Relevant concomitant care permitted or prohibited during the trial {11d}

Patients will continue the existing IOP-lowering regimen as prescribed before study enrollment. No additional IOP-lowering intervention will be provided unless a safety endpoint is reached (i.e., detection of VF progression, decrease in visual acuity ≥2 lines, or IOP > 30 mmHg on 2 consecutive visits). They are allowed to take other medications for medical conditions during the trial. Details of the medications used during the study period will be recorded and reported.

### Provisions for post-trial care {30}

The no-observed-adverse-effect-level of NR was 300 mg/kg/day [14]. We do not expect to observe any adverse effect with an oral intake of NR at 300 mg/day.

### Outcomes {12}

The primary outcome measure is the rate of change of average RNFL thickness measured by OCT over 24 months of study follow-up. Secondary outcome measures include (1) time to VF progression (possible or likely VF progression in GPA according to the EMGT criteria [21]) over 24 months expressed in survival probability, (2) time to progressive RNFL/GCIPL thinning (defined by Trend-based Progression Analysis [17, 18, 20]) over 24 months expressed in survival probability, and (3) the rate of change of VF sensitivity over 24 months (to investigate neuroprotection) and 1 month (to investigate neuroenhancement). Change in inner retinal vessel density over the parapapillary region and the macula measured by OCT angiography over 24 months will be evaluated as an exploratory outcome measure.

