### Sample size {14}

In our pilot study following 236 glaucoma patients every 4 months for ≥3 years, the mean rate of RNFL thinning was 1.2 μm/year (*P* < 0.001) for eyes with evidence of progressive RNFL thinning detected by TPA; the slope variance was 1.39 (μm/year)^2^ and the residual variance was 3.83 μm^2^ [20]. We aim to detect a difference of at least 0.7 μm/year in the rate of RNFL thinning between treatment groups, given that the mean rate of age-related RNFL thinning has been reported to be approximately 0.5 μm/year [22]. Taking reference from the method of sample size calculation for linear mixed modeling to compare the rates of change of a parameter of interest between two treatment groups described by Ard and Edland [23], 56 patients per study arm are needed for serial RNFL thickness measurements at baseline, 1 month, 4 months, and then every 2 months for 24 months (3 separate measurements will be collected at the baseline, 1-month, and 24-month follow-up visits) with a power of 80% and an alpha of 5%. Assuming a default rate of 10% during study follow-up, a total of 125 patients will be recruited.

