## Assignment of interventions: allocation

### Sequence generation {16a}

Patients will be randomly allocated (1:1) at the baseline visit to receive NR or placebo within 1 month of enrollment. Randomization with minimization by age (< 60 years vs ≥60 years), gender (male vs female), VF MD (<−6 dB vs ≥ −6 dB), spherical equivalent (<−6.0D vs ≥ −6.0D), mean IOP measurement over the past 3 years (≤21 mmHg vs > 21 mmHg), and number of glaucoma medications (0, 1, 2, 3, or ≥ 4) will be performed using an open-source computer program MinimPy [24]. A random element was introduced in the minimization procedure (i.e., weighted randomization of 0.8) to make the randomization more unpredictable [25]. If both eyes are eligible for inclusion, the one with smaller VF MD will be selected for randomization with minimization.

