## Data collection and management

### Plans for assessment and collection of outcomes {18a}

Patients will receive a clinical examination, OCT imaging of the RNFL, and VF testing at baseline, 1 month, 4 months, and then every 2 months for 24 months. Three repeated OCT and VF measurements will be collected at the baseline, 1-month, and 24-month visits.

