## Statistical methods

### Statistical methods for primary and secondary outcomes {20a}

(1) The rates of RNFL thinning (primary outcome measure) between treatment groups will be compared with linear mixed modeling after adjusting for covariates including age, axial length, glaucoma severity (baseline RNFL thickness), IOP levels during following up, OCT signal strength, multiple testing, and clustering between fellow eyes. (2) Change in VF sensitivity (measured in dB) at 1 month and the rate of change in VF sensitivity over 24 months between treatment groups will be compared with linear mixed models after adjusting for covariates. (3) Survival analysis will be performed to compare the differences in survival probabilities in (A) time from baseline to VF progression (determined by the EMGT criteria) and (B) time from baseline to progressive RNFL-GCIPL thinning (determined by TPA) between treatment groups using Cox proportional hazards models. One eye from each patient (the one selected for randomization with minimization) will be included in the analyses.

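### The secondary 24-month VF slope implicitly starts at the pre-treatment baseline, so it cannot isolate neuroprotection if the 1-month VF gain the trial also hypothesises occurs

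*Protocol article*

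**What the plan says.** All references are to the protocol article.

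- **Outcomes {12}** gives the VF rate two windows with two meanings: "the rate of change of VF sensitivity over 24 months (to investigate neuroprotection) and 1 month (to investigate neuroenhancement".
- **Trial design {8}** expects two effects from the same treatment. The early one is a gain: "an improvement in VF sensitivity could be detected in the NR-treated group at 1 month". The long-term one is on the rate: "a slower rate of VF sensitivity decline compared with those treated with placebo over 24 months".
- **Sequence generation {16a}** places allocation at baseline: "Patients will be randomly allocated (1:1) at the baseline visit to receive NR or placebo". The baseline VF tests are therefore pre-treatment.
- **Plans for assessment and collection of outcomes {18a}** sets the schedule: "Patients will receive a clinical examination, OCT imaging of the RNFL, and VF testing at baseline, 1 month, 4 months, and then every 2 months", ending at month 24. It adds: "Three repeated OCT and VF measurements will be collected at the baseline, 1-month, and 24-month visits".
- **Statistical methods for primary and secondary outcomes {20a}** compares "Change in VF sensitivity (measured in dB) at 1 month and the rate of change in VF sensitivity over 24 months" between arms by linear mixed models with covariates. It gives no slope origin later than baseline and no term for an early step.

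**The concern.** Neuroenhancement is a change in level and neuroprotection is a change in rate. The plan names them separately, but a straight line fitted from month 0 to month 24 responds to both. If VF sensitivity steps up between baseline and month 1 and stays up, the NR line tilts upward even when decline after month 1 is the same in both arms. If the gain appears at month 1 and then vanishes, the line tilts downward.

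What is at stake is the meaning of the 24-month VF slope. If the trial's own 1-month hypothesis is true, that slope no longer measures neuroprotection alone. The month-1 triplicate that could help separate the effects is already collected. It serves the 1-month comparison, but the text does not use it to separate step from slope.

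**Working it through.** **Inputs.** From {18a}: tests at months 0 (three), 1 (three), 4, 6, ..., 22 (ten single tests) and 24 (three), 19 in all. From Sample size {14}: RNFL slope variance 1.39 (μm/year)², residual variance 3.83 μm², target difference 0.7 μm/year, power 80%, alpha 5%, 56 per arm. The article gives no size for the VF gain and no VF variances.

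**Schedule.** Sum of times = 3 + 130 + 72 = 205 months, so the mean is 205/19 = 10.79 months = 0.899 year. Sum of squares = 3 + 2020 + 1728 = 3751. S = (3751 - 205²/19)/144 = 10.689 year².

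**The plan's own figure first.** Variance of a patient's slope = 1.39 + 3.83/10.689 = 1.748. n per arm = 2 × (1.960 + 0.842)² × 1.748/0.7² = 56.0, which matches the stated 56 with two-sided alpha. The RNFL sample size thus reproduces with a straight line that starts at baseline and uses the triplicates.

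**Sustained gain g complete by month 1, true rates equal.** The fitted slope shifts by g × Σ(t>0)(t - mean)/S = g × 3 × 0.899/10.689 = 0.252g per year. Gains of 0.5, 1 and 2 dB (assumed) add 0.126, 0.252 and 0.505 dB/year. With separate arm intercepts, a mixed model with random intercept and slope gives the same 0.252. A common intercept gives 0.254 to 0.265, depending on the assumed variances.

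**Gain present only at month 1.** Shift = g × 3 × (0.083 - 0.899)/10.689 = -0.229g per year.

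**Later starting points.**
- From month 1: 16 tests, S = (3751 - 205²/16)/144 = 7.809.
- From month 4: 13 tests, sum 202, sum of squares 3748, S = (3748 - 202²/13)/144 = 4.231.

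Shift in the fitted slope, dB/year per 1 dB of gain:

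| Shape of the gain | From month 0 | From month 1 | From month 4 |
|---|---|---|---|
| Complete by month 1, sustained | +0.252 | 0 | 0 |
| Half at month 1, full by month 4, sustained | +0.367 | +0.189 | 0 |
| Month 1 only | -0.229 | -0.378 | 0 |
| Full at month 1, fading linearly to zero at month 24 | -0.258 | -0.522 | -0.522 |

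The second row is the first minus half of the third: 0.252 + 0.5 × 0.229 = 0.367, and 0 + 0.5 × 0.378 = 0.189. In the last row the fade itself is 12/23 = 0.522 per year, which no choice of start removes.

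**Precision, using the RNFL variances as illustration.** From month 1: 1.39 + 3.83/7.809 = 1.880, and 1.880/1.748 = 1.076, so variance is 7.6% higher. That corresponds to 60.2 against 56.0 per arm, or power at 56 per arm of 77.1% against 80.0%. From month 4: 1.39 + 3.83/4.231 = 2.295, and 2.295/1.748 = 1.31, so variance is 31% higher.

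**Scale under assumed VF variances.** Assume a slope SD of 0.5 to 1.0 dB/year and a residual SD of 1.0 to 1.5 dB. With 56 per arm and equal true rates, a sustained 1 dB gain gives a 23% to 63% chance of a significant result for slower decline, against a nominal 2.5% in that direction. For a 0.5 dB gain the range is 9% to 21%.

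**The case against.** The strongest reply has four parts.

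**The model is not spelled out.** The article says linear mixed models and no more. Slope origin and step terms are details that a statistical analysis plan may hold. This stands in part: the baseline start is inferred. But the outcome definition itself fixes a 24-month window and its interpretation, and with a last visit at month 24 that window has to begin at baseline.

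**The early gain will be seen anyway.** The 1-month comparison is reported separately, so a reader would have the step beside the slope. This is true and softens the point. It does not make the slope an estimate of neuroprotection.

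**The direction is assumed.** No document says that a gain would last. This stands: the sign of the shift depends on persistence, so the point cannot be that the plan favours NR.

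**The remedy is imperfect.** It removes the shift only for a gain complete by month 1 and sustained. For a gain seen only at month 1 the later start does worse (-0.378 against -0.229). This also stands. It is why the later slope should be read together with the baseline-start slope and not simply replace it.

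A reader might also infer that a drug with only a symptomatic effect would be declared neuroprotective. The documents do not support that. The primary outcome is the RNFL rate, the VF slope is part of the third secondary outcome, and a VF-only gain does not by itself move the primary.

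**Conclusion.** The point holds for the secondary 24-month VF slope. A sustained gain complete by month 1 adds about 0.25 dB/year per 1 dB to the fitted slope difference with no change in the true rate of decline; a gain confined to month 1 shifts it by about -0.23 dB/year per 1 dB. These per-dB figures follow from the schedule and a baseline-start line. The size of any gain, its persistence and the VF variances are assumptions.

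Three extensions may tempt a reader and should not be drawn.
- **Primary RNFL slope:** the article hypothesises a 1-month gain for VF only, so an early RNFL step would be invented.
- **Time to VF progression:** the article does not say which fields form the reference for the progression criteria, so the same fault cannot be shown there.
- **Interim looks:** Interim analyses {21b} provides for stopping only if NR is significantly worse, and makes no neuroprotection claim.

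This is an inexpensive improvement to one secondary analysis and no threat to the trial's main conclusion.

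**What to change.** In the VF mixed model, add a treatment-by-post-baseline step term alongside treatment-by-time. With arm-specific intercepts this is equivalent to estimating the slope from the month-1 triplicate onward. Then:

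1. Report the step as the neuroenhancement estimate and the accompanying slope as the neuroprotection estimate. State that this separation assumes the early gain is complete by month 1 and persists.
2. Report the baseline-start slope as well, and base any VF claim of neuroprotection on agreement between the two.
3. Add a slope from month 4 as a check for a gain that is still building, or already gone, after month 1. State that a gain fading slowly over the whole period cannot be separated from decline by any start point.

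This changes analysis wording only and adds no visit, test or patient. It should be fixed before unblinding. The cost is precision: slope variance about 7.6% higher from month 1 with the RNFL variances as illustration. The month-4 slope is about 31% more variable on the same basis, so it suits a check and not the main estimate. The VF figures should be recomputed once VF variances are available.
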